### Objective

The overall objective of this study is to implement the PROMPT-Care 2.0 eHealth platform and determine its efficacy among cancer patients at four tertiary hospitals. Specifically, this study will test whether web-based routine collection of PROs, combined with automated alerts to clinical teams and provision of patient self-management resources, result in reduced emergency department presentations, and improved chemotherapy delivery and health service referrals. The study will also evaluate system utility and potential benefits and barriers to PROMPT-Care implementation in routine care from both the patient and healthcare professional perspective.

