#### Patient clinical and socio-demographic characteristics

Upon consenting, participants will complete a questionnaire about socio-demographics including: marital status, education level, employment status and language spoken at home. Additional demographics (eg. age, gender and need for interpreter) and clinical characteristics such as date of diagnosis, site (ICD-10), stage (TNM classification) and treatment details will be extracted from the OIS.

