### Sample size

A minimum sample size of 1760 (352 intervention and 1408 control) patients is required to detect a 14% reduction in the number of ED presentations in the PROMPT-Care group compared with the control group. This is based on the assumed rate of ED presentations being 1.4 visits per patient during the study period, a 1:4 ratio of PROMPT-Care to control group patients, 80% power and 5% statistical significance.

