### Statistical analyses

Descriptive statistics will be generated for all socio-demographic and clinical characteristics, and outcome measures. A multivariable Poisson or negative binomial regression (depending on over-dispersion) will be used to determine whether the rates of ED presentations were different between the PROMPT-Care and control groups adjusting for covariates (such as age, sex, stage of disease, and treatment status). Number of referrals to allied health services will be analysed similarly. Multivariable Cox proportional hazards model will be used to analyse length of time from start to end of chemotherapy adjusting for covariates.

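### The primary model compares volunteers with unmatched database controls but does not commit to hospital, tumour site, time since diagnosis or prior ED use, although moderate residual confounding could mimic part or all of a 14% effect

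*Protocol article*

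**What the plan says.** The Objective of the Protocol article is to "determine its efficacy among cancer patients at four tertiary hospitals". The groups are not randomised. Under Study population and Patient identification and consent, intervention patients are identified by participating clinicians, invited, and consent. They must be able to complete the survey in English, have Internet access outside the clinic, and not have a blood cancer. Under Control population, controls are taken from hospital databases of patients seen at the centres during the study period. No matching is described and none of those criteria is repeated.

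Statistical analyses specifies Poisson or negative binomial regression for ED presentations, "adjusting for covariates (such as age, sex, stage of disease, and treatment status").

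The data available are described in two places. Outcomes (with Table 1) takes ED presentations from the electronic medical record and defines the outcome over the study period; no earlier ED history is mentioned. The section on patient characteristics says: "Upon consenting, participants will complete a questionnaire about socio-demographics including: marital status, education level, employment status and language spoken at home". The same paragraph takes age, gender, interpreter need, date of diagnosis, ICD-10 site, stage and treatment details from the oncology information system.

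Sample size plans to "detect a 14% reduction in the number of ED presentations in the PROMPT-Care group compared with the control group". The calculation takes "the assumed rate of ED presentations being 1.4 visits per patient during the study period". It uses four controls for each intervention patient, with "80% power and 5% statistical significance".

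**The concern.** With no randomisation and no matching, the regression covariates carry the whole causal claim. The four named factors are generic. The article itself gives reasons to expect imbalance on others:

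- **Tumour site.** Blood cancers are excluded from the intervention group and not, as written, from the controls.
- **Hospital.** Recruitment depends on which clinicians take part, and the alert pathway is agreed centre by centre. No balance of controls by site is stated.
- **Time since diagnosis.** Recruitment aims for similar proportions of patients in active treatment and in follow-up. The control extract has no such aim. Treatment status covers part of this, but not all.
- **Prior ED use.** This is the most direct measure of a patient's tendency to attend ED, and the planned extraction does not reach back to it.

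Marital status, education, employment and home language cannot fill the gap. They come from a questionnaire given on consent, so database controls have no values.

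If the groups differ in underlying ED use after adjustment, a rate ratio below 1 cannot be attributed to PROMPT-Care, and one near 1 could hide a real effect.

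**Working it through.** **Inputs from Sample size.** Control rate 1.4 visits per patient; 14% reduction, so the intervention rate is 1.4 × 0.86 = 1.204; ratio 1:4; 80% power; 5% significance, sidedness not stated (two-sided reproduces the total, one-sided does not).

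**Step 1: reproduce the plan's figure.** For a Poisson Wald test on the log rate ratio,

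n(intervention) = (1.960 + 0.842)² × [1/1.204 + 1/(4 × 1.4)] / (ln 0.86)² = 7.849 × (0.8306 + 0.1786) / 0.02275 = 348.2.

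That is 349 + 1,396 = 1,745, which is 0.9% below the stated 1,760. With 352 and 1,408 patients the Poisson power is 80.4%. The planned size is therefore consistent with a rate ratio of 0.86 and Poisson variation.

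**Step 2: how much confounding equals the target effect.** Suppose there is no true effect and one unadjusted binary factor multiplies ED use by R. If a proportion p1 of volunteers and p0 of controls have it, the expected rate ratio is [1 + p1(R − 1)] / [1 + p0(R − 1)]. The documents give no value for R, p1 or p0, so all of these are assumptions, and they describe imbalance left after adjustment for the named covariates.

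| R | p0 (controls) | p1 (volunteers) | Spurious rate ratio |
|---|---|---|---|
| 1.5 | 40% | 30% | 1.15/1.20 = 0.96 |
| 1.5 | 40% | 20% | 1.10/1.20 = 0.92 |
| 2 | 40% | 30% | 1.30/1.40 = 0.93 |
| 2 | 40% | 20% | 1.20/1.40 = 0.86 |
| 3 | 40% | 30% | 1.60/1.80 = 0.89 |
| 3 | 40% | 20% | 1.40/1.80 = 0.78 |

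A weak factor cannot do it: with R = 1.25 no imbalance reaches 0.86 for a control prevalence up to 60%. If volunteers hold the factor more often, the bias reverses: R = 2 with 50% against 40% gives 1.5/1.4 = 1.07.

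The E-value gives the same message without prevalences. With 1/0.86 = 1.163, it is 1.163 + √(1.163 × 0.163) = 1.60. A factor associated with both group and ED use by ratios of about 1.6 each could account for the full target effect.

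**Step 3: what the test would then do.** With 352 and 1,408 patients and no true effect, the chance of a significant result (two-sided 5%) is:

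| Residual bias (rate ratio) | Poisson | Negative binomial, dispersion 1 (assumed) |
|---|---|---|
| 0.95 | 17% | 10% |
| 0.93 | 29% | 15% |
| 0.90 | 52% | 26% |
| 0.86 | 80% | 47% |

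**Step 4: possible gain in precision.** Assume dispersion 1 and an ED propensity that stays the same before and after the index date. Conditioning on a prior period with mean m leaves a dispersion of about 1/(1 + m): 0.59 for m = 0.7 and 0.42 for m = 1.4. Power at a rate ratio of 0.86 rises from 47% to 57% and 63%. This is a best case, since patients with a recent diagnosis may have a look-back that precedes their cancer.

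**The case against.** The strongest reply is that the covariate list is introduced as examples. Nothing is excluded, and a condensed article may leave the final list to a full protocol or analysis plan that is not shown. This stands: a reader might infer that the four factors have been left out of the model, and the text does not support that. The reply does not answer the data question. The article describes ED extraction for the study period only, so prior ED use would not be available to the model unless that extraction is widened.

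A reader might also infer that all four factors are held for both groups. That is not stated. Site and diagnosis date appear in a paragraph about participants, the article does not say what is extracted for controls, and earlier ED use is only an inference from the record that supplies the outcome. Hospital can reasonably be inferred.

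A third tempting reading is that self-selection accounts for the whole 14%, or that volunteers use ED less to begin with. Neither is shown. The prevalences and strengths above are assumed, smaller imbalances explain only part of the effect, and stage and treatment status may already absorb some of it. In-clinic recruitment and the aim of balancing treatment and follow-up patients could push the crude bias the other way.

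**Conclusion.** The concern holds in a limited form. The design rests on regression adjustment alone, the article does not commit to four plausible confounders, and its ED extraction as described would not supply the most informative of them. Because the target is a rate ratio of 0.86, moderate residual confounding (E-value 1.60) could mimic part or all of it. For a twofold risk factor held by 40% of controls, the spurious rate ratio is 0.93 or 0.86 when 30% or 20% of volunteers have it. These are conditional illustrations in one direction; the true size and direction are unknown. The power gain in step 4 is a possible side benefit that depends on the assumed dispersion and on stable ED propensity. The change is worth making because it is cheap, but it would reduce self-selection bias and not remove it.

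**What to change.** 1. Extend the ED extraction to a fixed look-back, for example 12 months, before consent. Define a comparable index date for controls.
2. Commit in advance to a primary model with pre-index ED count (with look-back length), hospital, tumour group and time since diagnosis, alongside age, sex, stage and treatment status, where the data are held for both groups. State which are held.
3. Apply the blood-cancer exclusion to controls. Restrict controls on interpreter need instead of adjusting for it: intervention patients must complete the survey in English, so overlap may be small.
4. Report the pre-index ED rate ratio between groups, adjusted for the other covariates but not for prior ED count, as a diagnostic of remaining selection. With prior count in the same model the check would be circular.

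The cost is a longer extraction from the same record and a few model terms. Newly arrived patients will have a short look-back, which is why its length must be included. Motivation and Internet access are not described as measured in controls, so confounding by them would remain and should be stated as a limitation.

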### Study population

#### Patients

Eligible patients are people who are either currently receiving cancer care (including follow-up care) or have recently been diagnosed with cancer and are scheduled to commence cancer treatment at one of the four participating sites. Eligibility criteria include a confirmed diagnosis of cancer, age 18 years or over, cognitively able to provide informed consent and understand the surveys, and ability to complete the survey in English. Exclusion criteria are having a diagnosis of a blood cancer and not having access to the Internet outside of the clinic.

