### Control population

A list of potential control individuals (minimum *n* = 1408) will be extracted from hospital databases of the general cancer patient population who were seen at the participating cancer therapy centres during the study period.

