#### Patient identification and consent

Participating clinicians will review their clinic lists to identify eligible patients who have appointments scheduled within the coming two (2) months. Two patient recruitment approaches will be utilised to achieve a similar proportion of both patients in active treatment and those in follow-up care.

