##### In clinic

Eligible patients attending a cancer care clinic will be invited to participate by a member of the clinical trial team in the waiting area. The trial research member will explain the study in detail and provide patients with a study pack containing a letter of invitation, participant information and consent form, demographics survey and reply-paid envelope. Consenting patients will be asked to complete a consent form and their first PROMPT-Care assessment just prior to their appointment.

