#### Assessment completion

Patients will complete PROMPT-Care assessments on a monthly basis and will be followed up for a minimum of four months. Patients will have the option to complete assessments either at the hospital in clinic, their home or any public community location. Patients completing assessments in clinic will be provided with a tablet device in the waiting area just prior to their scheduled appointment. Patients who complete assessments from home or in community locations will receive an email containing the survey link three days before their assessment is due.

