### Measures

#### Outcomes

The primary outcome is number of emergency department (ED) presentations observed during the study period. Details about ED presentation dates, reason for presentation and any resulting admissions will be extracted from the electronic medical record (EMR) (Table 1).

**Table 1 Tab1:** Primary and secondary outcome data collected

Data	Description of data	Source of data
Primary Outcomes		
Emergency Department (ED) presentations	• ED presentations (date, number of visits) • Length of stay • Reason for presentation	Extracted from electronic medical record (EMR)
Secondary Outcomes		
Time on chemotherapy	• Planned chemotherapy regimen • Actual regimen start and end date • Toxicities, changes to treatment delivery and reasons	Extracted from oncology information system (OIS)
Referral to allied health services	• Date of referral and allied health service type • Reason for referral eg. emotional distress, case management etc.	Extracted from EMR & OIS

The secondary outcomes are time receiving active chemotherapy and referrals to allied health services. Details of planned and actual chemotherapy regimens as well as any toxicities and changes to treatment delivery will be extracted from the OIS. Date, reason and number of referrals to allied health services will be tabulated and extracted from the medical record and OIS.

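### Chemotherapy duration is timed from chemotherapy start although intervention patients may consent mid-course; the hazard ratio is biased, with size and sign depending on facts the protocol does not give

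*Protocol article*

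**What the plan says.** The analysis is stated under Statistical analyses: "Multivariable Cox proportional hazards model will be used to analyse length of time from start to end of chemotherapy adjusting for covariates". The outcome table lists the data for it as "Actual regimen start and end date", taken from the oncology information system. The date of consent plays no part in either place.

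Three other sections determine who enters this analysis, and when.

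- **Patients:** "Eligible patients are people who are either currently receiving cancer care (including follow-up care) or have recently been diagnosed with cancer". The newly diagnosed group is awaiting treatment; the other group may be at any point of care.
- **Patient identification and consent:** "Two patient recruitment approaches will be utilised to achieve a similar proportion of both patients in active treatment and those in follow-up care". Under In clinic, exposure begins at a clinic visit: "Consenting patients will be asked to complete a consent form and their first PROMPT-Care assessment just prior to their appointment". Neither section ties consent to the start of a course.
- **Control population:** potential controls are people "who were seen at the participating cancer therapy centres during the study period". No date corresponding to consent is given for them.

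**The concern.** Take a patient recruited in week 12 of chemotherapy. That patient could not have stopped before week 12, or there would have been no course to be recruited from. Those 12 weeks are event-free by design and precede any use of PROMPT-Care. A Cox model of start-to-end duration nevertheless counts them as time at risk in the intervention group. Patients found mid-course also tend to have longer courses, because a long course offers more visits at which to be recruited.

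Age, sex, stage and treatment status, the covariates the article gives as examples, do not record how long a patient had already been on chemotherapy at entry, so adjusting for them leaves the problem in place.

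The Background presents longer tolerability of chemotherapy as a benefit, and the Objective includes better chemotherapy delivery. An HR below 1 for ending chemotherapy would therefore be read as efficacy. With non-randomised controls, nothing in the design makes the two groups' entry times alike.

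**Working it through.** The article gives no figure for this outcome (its sample size concerns emergency department presentations), so there is none to reproduce. The check is a simulation with no true effect (HR = 1).

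**Inputs from the article.** Time axis, eligibility, consent and control source as above. Intervention patients "will be followed up for a minimum of four months". The groups are 352 and 1408, with active treatment and follow-up in similar proportion.

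**Assumptions.** Half of each group contributes a course: 0.5 × 352 = 176 and 0.5 × 1408 = 704. Mean course 5 months; Weibull durations with shape 1 (very variable) or 2.5 (less so). Study period 18 months, with enrolment spread over the first 18 − 4 = 14. No covariates; 200 replicates per cell.

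**Step 1: length bias.** If courses are sampled while in progress, their mean length is mean × (1 + CV²), where CV² = Γ(1 + 2/k)/Γ(1 + 1/k)² − 1 for Weibull shape k.

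- k = 1: CV² = 1, so 5 × 2 = 10 months.
- k = 2.5: CV² = 0.183, so 5 × 1.183 = 5.9 months.

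The excess over 5 months arises from sampling alone.

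**Step 2: Cox HR timed from chemotherapy start, true HR = 1.** Each cell shows shape 1 / shape 2.5.

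| Intervention courses joined mid-course | Controls starting chemotherapy in the period | Controls on chemotherapy at any time in the period |
|---|---|---|
| 0% | 1.00 / 1.01 | 1.28 / 1.12 |
| 25% | 0.73 / 0.87 | 0.93 / 0.97 |
| 50% | 0.59 / 0.79 | 0.75 / 0.88 |
| 75% | 0.48 / 0.74 | 0.64 / 0.82 |
| 100% | 0.41 / 0.68 | 0.57 / 0.78 |

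In the right-hand column, controls whose course began before the period carry guaranteed time of their own. This weakens the bias and, with few mid-course intervention patients, reverses it.

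**Step 3: other settings.** With recruitment over 12 months and controls on chemotherapy at any time in the period, the HR at 0 / 10 / 25 / 50 / 83% mid-course is:

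- shape 1: 1.30 / 1.11 / 0.98 / 0.79 / 0.65
- shape 2.5: 1.17 / 1.09 / 1.04 / 0.91 / 0.80
- shape 6 (courses of nearly fixed length): 1.03 / 1.00 / 1.02 / 0.96 / 0.91

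A further set of null runs, varying control sampling and course shape, gave 0.47 to 0.83 at 83%, 0.75 to 0.99 at 25% and 0.97 to 1.35 at 0%.

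**Step 4: the same data with delayed entry.** Risk time runs from consent for intervention patients and from the control's own entry date. For the cells of Step 2 the HR is then 0.99 to 1.01. In the further set of runs it was about 0.90 to 1.07.

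**The case against.** The best reply is that the sentence names an interval and a model but does not say when a patient enters the risk set. Chemotherapy start is a legitimate time scale, and the remedy keeps it. The analysis could also be limited to regimens begun after enrolment, which would fit the listed data. On this view the article is merely silent on details left to a fuller document.

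Part of this stands: the sentence is compatible with the fix. But it does fix the analysed time as the whole course. Followed as written, with eligibility that admits patients mid-course, it counts pre-consent time. The point is a specific change to a stated analysis.

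Three further objections stand, and they limit the claim.

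- **Direction.** A reader might infer that the HR must come out spuriously favourable. The documents do not support this: with few mid-course patients the bias can be absent or go against the intervention.
- **Size.** A reader might settle on an HR of 0.65 to 0.73, which some null simulations give. That range assumes about 83% of intervention patients are already on chemotherapy at consent, and no section gives such a share. Active treatment also includes radiotherapy, and patients who have not yet started treatment are eligible.
- **Controls.** A reader might infer that controls escape any similar condition. They must have been seen in the study period, so some carry guaranteed time too, and the text describes only a list of potential controls. Had controls been sampled on chemotherapy at a matched index date, the bias would vanish with all intervention patients mid-course (HR 0.99 to 1.00) and otherwise reverse (1.06 to 3.1). The article describes no such sampling.

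**Conclusion.** The point holds in conditional form. As written, the analysis counts unexposed, event-free time before consent as intervention risk time, and covariate adjustment does not correct it. Under no true effect, with an assumed 5-month mean course and 18-month window, the HR is about 0.5 to 0.8 at 83% mid-course, about 0.75 to 1.0 at 25% and about 1.0 to 1.35 at 0%. Courses of nearly fixed length bring it closer to 1 (0.91 at 83%). The bias favours the intervention when a substantial share enrols mid-course. The mid-course share, the variability of course length and the control sampling drive both size and sign, and the article gives none of them, so these figures are a range under assumptions and not a prediction. The outcome is secondary; the emergency department analysis and the sample size are untouched. The change should be made before the data are analysed.

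**What to change.** Keep time since chemotherapy start as the scale. Enter each patient in the risk set, by left truncation, at the later of chemotherapy start and consent (intervention) or a comparably defined index date (control). Count only control courses that are ongoing at, or start after, that index date. State how the index date is assigned. As a sensitivity analysis, restrict both groups to courses starting on or after consent or index date. Report the share of intervention courses already in progress at consent, since it governs how far the two analyses could differ.

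The cost is one entry-time variable in the Cox model, the work of assigning a control index date, and some loss of precision from dropping time before entry. No further patients are needed and patient care does not change.

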## Discussion

To date, the impact of collecting and utilising PROs in the oncology setting have been studies in defined groups of patients. The results from this study will contribute important new evidence to the literature, with its inclusion of a broad population of patients who are currently undergoing cancer treatment or are in follow-up, and patients with a wide range of tumour types. PROMPT-Care Version 1.0 has previously been demonstrated to be feasible and acceptable [14, 15]. This project will provide evidence regarding the impact of the expanded and improved PROMPT-Care Version 2.0 system on healthcare utilisation, including emergency department presentations, chemotherapy adherence and referral to allied health services; the acceptability of the tailored, stepped self-management resources; and usefulness of newly introduced strategies to facilitate shared follow-up care - the Treatment Summary and SCPs.

This information will be used to guide further revisions of the PROMPT-Care system and aid its wider implementation in other cancer centres in Australia; and inform its potential as an alternative model of providing ongoing patient supportive care. The resulting eHealth platform will be an evidence-informed tool which supports and enables cancer patients to achieve and maintain improved well-being and better cancer outcomes.

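### The Cox outcome for chemotherapy is raw start-to-end time, which does not separate planned completion from early stopping, so its hazard ratio is not interpretable as improved delivery or adherence

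*Protocol article*

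**What the plan says.** All references are to the protocol article; no separate analysis plan is at hand.

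- **Outcomes** names the endpoint as a duration: "The secondary outcomes are time receiving active chemotherapy and referrals to allied health services".
- **Statistical analyses** gives the model in one sentence: a covariate-adjusted Cox model will be used to "analyse length of time from start to end of chemotherapy". It states no event or censoring rule. The covariates named as examples for the emergency department model are age, sex, stage and treatment status; regimen and planned duration are not among them.
- **Table 1** lists, for this outcome, the planned regimen, the actual start and end dates, and "Toxicities, changes to treatment delivery and reasons".
- **Objective** says the trial tests for "improved chemotherapy delivery and health service referrals". The **Discussion** describes the same outcome as part of "chemotherapy adherence and referral to allied health services".
- No direction of benefit is stated for time on chemotherapy. The Background reports earlier work in which patients tolerated chemotherapy for longer, and that is the only hint.
- **Study population** admits all cancers except blood cancers, on treatment or in follow-up, with no limit on treatment intent. **Control population** takes controls from hospital databases; allocation is not randomised.

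**The concern.** The endpoint and the aim do not match. Delivery and adherence compare what was given with what was planned. Start-to-end time makes no such comparison. If the end of chemotherapy is the event, a patient who finishes a fixed course on schedule and one who stops midway for toxicity both have it. Planned completions, which the intervention is not meant to change, then mix with the early stops that it might prevent. A course stretched by delays gives a longer time than the same course given on schedule.

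Planned lengths are likely to vary across so broad a population, and nothing in the design forces regimen mix to balance between consenting intervention patients and database controls. At stake is one of the two secondary outcomes: the trial could report a hazard ratio for chemotherapy that readers take as evidence about delivery when it is not.

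**Working it through.** **The plan's own figure.** No sample size, event count or power is given for this outcome. The only figure is for the primary outcome, and it reproduces. With a Poisson comparison on the log rate ratio, two-sided 5% and 80% power, intervention n = (1.960 + 0.842)² × [1/(1.4 × 0.86) + 1/(4 × 1.4)] / (ln 0.86)² = 348.2. That gives 349 + 1396 = 1745, against the stated 1760. It has no bearing on this point.

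The documents give no chemotherapy inputs, so everything below is illustration on assumed values.

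**1. Dilution.** Assumed: unplanned stopping is exponential at 0.06 per month in control and 0.042 in intervention (ratio 0.70, the true effect). A share *f* of patients has a fixed course with planned length uniform on 3 to 6 months; the rest are open-ended. Follow-up is cut at 12 months, and allocation is 1:4.

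Event shares at *f* = 0.6:
- Every fixed course has ended by 6 months. Open-ended courses end within 12 months with probability 1 − exp(−0.72) = 0.513 (control) and 1 − exp(−0.504) = 0.396 (intervention).
- Any end: control 0.6 + 0.4 × 0.513 = 0.805; intervention 0.6 + 0.4 × 0.396 = 0.758; pooled 0.8 × 0.805 + 0.2 × 0.758 = 0.796.
- Unplanned stop within a fixed course: control 1 − [exp(−0.18) − exp(−0.36)]/0.18 = 0.236; intervention 1 − [exp(−0.126) − exp(−0.252)]/0.126 = 0.172. Overall: control 0.6 × 0.236 + 0.4 × 0.513 = 0.347; intervention 0.6 × 0.172 + 0.4 × 0.396 = 0.261; pooled 0.8 × 0.347 + 0.2 × 0.261 = 0.330.
- So (0.796 − 0.330)/0.796, about 59% of any-end events, are planned completions.

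Simulated Cox hazard ratios with any end as the event: about 0.76 to 0.77 at *f* = 20%, 0.87 at 60%, and 0.91 to 0.92 at 90%. With unplanned stopping as the event: about 0.70 throughout. Stratifying by fixed versus open-ended course at *f* = 60% leaves the any-end value at about 0.87, so this dilution comes from planned completions and not from imbalance in mix.

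**2. Delays alone.** Same model, equal stopping rates, fixed courses 15% longer in the intervention group: any-end hazard ratio about 0.89 to 0.92; unplanned-stop about 1.0.

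**3. Mix alone.** Equal stopping rates, fixed courses in 50% of intervention and 60% of control patients, no adjustment: any-end about 0.87 to 0.89; unplanned-stop 1.00. Stratifying by course type removes this bias.

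**4. Direction.** Assumed: everyone is planned six 3-weekly cycles. Before each of cycles 2 to 6 the patient may stop, or may continue with a one-week delay. There are 8000 control and 2000 intervention patients. Hazard ratios are any end, then early stop with completion censored:
- More delays only (30% v 10% per cycle; stopping 5% in both): 0.42; 0.96.
- Fewer early stops only (3% v 6%; delays 15% in both): 0.83; 0.46.
- Fewer stops and fewer delays (3% v 6%; 10% v 25%): 1.68; 0.53.
- Fewer delays only (10% v 30%; stopping 5% in both): 2.25; 1.07.

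A repeat at four times the size, averaged over four runs, moved no value by more than 0.06. These effects are large because everyone shares one course length. What carries over is the sign, not the size.

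**The case against.** The strongest reply is that the article never says any end of chemotherapy is the event. Event and censoring rules usually sit in an analysis plan, which is not shown, and Table 1 collects what a better definition needs. This stands in part. The event is inferred, and its absence from a journal article is no fault. But the article does state the quantity, twice, as a duration from start to end. A plan that used early cessation would be changing the published endpoint, not filling it in.

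Three stronger readings are tempting, and the documents do not support them.

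- A reader might infer that the analysis *cannot* show better delivery. When only early stopping falls, the any-end hazard ratio still moves the right way (0.87 and 0.83 above). That is dilution, not blindness.
- A reader might infer that the hazard ratio *mainly* reflects regimen mix. With equal mix in both groups, stratification changes nothing. Mix biases the result only if the groups differ and the model does not adjust for it, and the covariate list is open-ended.
- A reader might infer that the plan *counts* delays as benefit. That requires longer to be better, which the article only implies through cited background. If shorter were better, early stopping would score as benefit, so neither direction rescues the measure.

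**Conclusion.** The point holds as a mismatch between endpoint and aim. As written, the Cox analysis does not separate planned completion from early discontinuation or compare actual with planned treatment, so its hazard ratio should not be read as delivery or adherence.

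The conclusion rests on the plain reading that the end of chemotherapy is the event. On that reading a true 30% reduction in early stopping would appear as roughly 8% to 24% (hazard ratio about 0.92 to 0.76), depending on the share of fixed courses. Where delays also change, and longer is taken as better, the result can reverse: fewer stops and fewer delays gave 1.68. All sizes depend on assumed stopping rates, course lengths and horizon; the mechanism does not. Confidence is moderate, because a fuller document may define the event. The change should be made, but it concerns a secondary outcome only.

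**What to change.** Replace the start-to-end duration with an outcome tied to the plan, using items already in Table 1:

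- Event: cessation before the planned course is complete, identified from planned regimen, actual dates and recorded reasons. For courses without a planned end, state which recorded reasons count.
- Censor at planned completion, and at end of follow-up for patients still on treatment.
- State whether death on treatment is an event or a competing event.
- Adjust for, or stratify by, planned duration or treatment intent.
- Report actual over planned duration separately, so that delays are visible and not mixed into the hazard ratio.
- State the direction of benefit for each measure.

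The cost is a derived variable, some wording, and fewer events: about 33% of chemotherapy patients instead of 80% in the illustration at 60% fixed courses. Fewer events need not mean less power. Information is roughly proportional to event share × (ln HR)²: 0.33 × (ln 0.70)² = 0.042 for early cessation, against 0.80 × (ln 0.87)² = 0.016 for any end. Adjusting for planned duration while keeping any end as the event would deal with regimen mix, but not with dilution or delays. The primary outcome and its sample size are untouched.
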